#### Functionality appreciation

An adapted version of a measure used by Swami et al. [47] and Dohnt and Tiggemann [45] among a similar age group will be used to measure functionality appreciation. The measure is open-ended and asks children to; *‘tell me all the amazing things you can do with your body’*. In line with Swami et al. [47] and Dohnt and Tiggemann [45] children will be allowed to respond with as many answers as they wish. The moderator will ask the question then will turn over a 60-second sand timer. Children can respond with as many answers as possible before the sand runs out. If a child is still talking when the sand timer had finished, they are allowed to continue until they coame to a natural stop. Responses will be recorded verbatim.

This measure has been refined through several rounds of public involvement with children, teachers, and parents. The wording used by Swami et al. [47] and Dohnt and Tiggemann [45] differed slightly as their questions directly related to the theme of the intervention being tested. For example, Swami et al. [47], who evaluated a theatre production of Cinderella *(‘Cinderella: the AWESOME truth’*) which encouraged children to recognise their own awesome and unique qualities, asked children to list *‘what is unique about you?*’. Dohnt and Tiggemann [45] who evaluated a positive body image storybook focusing on special talents asked children to list ‘*what special talents do you have?*’. Our interventions encourage children to recognise the amazing things their body can do. Therefore, we tested the following item with our public involvement group for comprehension; ‘*tell me as many things as possible that your body can do. You can say things that happen inside your body or things different body parts can do – you can say anything your body does for you!’.* These instructions were evidently too lengthy. Consequently, a simplification of the wording was implemented with the addition of the term ‘amazing’ to qualify responses. An absolute count score will be calculated, with a higher number of responses indicating higher functionality appreciation. In addition, content analysis will be conducted, exploring the content of children’s answers to strengthen the interpretation of our findings.

This measure will be called ‘Time’ to the participating children.

#### Weight bias

To measure weight bias in children aged 4–6 years, existing measures developed by Parnell et al. [62] and Damiano and colleagues [63] for use among young children were adapted. Children will be asked to rate both a smaller and a larger child (matched on ethnicity and gender; see Fig. 3) on a 3-point scale containing two bipolar adjectives or phrases. There will be five pairs in total, presented in the same order each time; very clever/not clever at all, cute/ugly, has no friends/has lots of friends, active/not very active and good at dancing/not good at dancing.

**Fig. 3 Fig3:**
[figure not shown]
Weight bias measure - 'pictures'

The child images were created by illustrator, [name], for the purpose of this study. [name] previously worked with Parnell et al. [62] and Matheson et al. [46] to develop a set of child images to assess appearance stigma among primary school children and 7–14-year-olds, respectively. For the present study, there will be three sets of made-up images in total that broadly represent three ethnic groups: Black girl and boy, South Asian girl and boy, and White girl and boy. These groups were chosen as they represent the three largest ethnic groups in the UK [64]. Each set of images includes a smaller and a larger child dressed in the same clothes (e.g., plain t-shirt and jeans with white trainers). They are stood up straight, hands by their sides with a slight smile on their face.

The response scale for this measure was reduced from a 7-point [63] to a 3-point ordinal scale, ranging from 1 = *child rates the image positively*, to 3 = *child rates the image negatively.* The middle option, a score of 2, is given when a child rates the child image *as ‘somewhere in the middle’*, indicating a *neutral* response. A total score will be calculated by the mean difference between smaller and larger child, with higher scores reflecting higher weight bias.

This measure will be called ‘Pictures’ to the participating children.

### Intervention acceptability

We will also examine child and parent intervention acceptability across all conditions at post-intervention (T2).

Children will be asked three acceptability questions. Children will respond using the same rectangles and circles as per our body appreciation measure to the question: ‘*did you like the [episode/music video] you just watched?*’ whereby children stand on a ‘start’ rectangle and the moderator will ask them to respond, ‘*yes’* or ‘*no’*. If the child responds yes, they will be asked ‘how much’ using three response options: ‘*a little bit’* (smallest circle*)*, ‘*a medium bit*’ (medium circle), or ‘*a lot*’ (biggest circle). They will be encouraged to expand on their answer giving details of what they did/did not like.

To check children’s familiarity with the media content, we will also ask children to answer; ‘*yes’* or ‘*no’* to; *‘have you seen this [episode/music video] before?’*. Finally, children will be asked an open-ended question to explore their learnings from the content they watched; ‘*did you learn anything while watching the [episode/music video]?’.*

Parents will complete a paper-based questionnaire containing questions related to the content they watched. Parents will be asked; ‘*how much did you like the episode/music video?’* with responses on a 5-point scale ranging from 1 *= did not like it at all* to 5 = *liked it very much.* They will also respond to; *‘Do you think this message is important for your child to learn at their age?’* and *‘Would you recommend this episode/music video to other parents of children of a similar age?* on a 3-point scale *yes*,* no* or *unsure.* Several open-ended questions will allow parents to expand on their answers (e.g., things they *did/did not* like).

#### Repeat watching

In between post-intervention (T2) and follow-up (T3), parents will be given access to their assigned media content via a secure link and encouraged to rewatch it with their child before they return for their next session in approximately seven-ten days’ time. Parent’s will self-report how many times they re-watched their content in their T3 follow-up survey.

#### Child interview moderator fidelity

All children’s interviews (T1, T2 and T3) will be audio recorded for the purpose of assessing moderator’s adherence to and competency in delivering the child interviews across each timepoint. The adherence checklist will align directly with the child interview protocol which all moderators have received training on. Moderators will also be rated on seven dimensions of competency (e.g., organisation, communication and expression, friendliness).

Overall, the pilot study will involve interviews with 80 children across three timepoints (total of 240 interviews) and the larger scale RCT will involve interviews with 440 children across three timepoints (total of 1320 interviews). 20% of interviews from the pilot (i.e., 48 interviews) and 10% of interviews from the main RCT (i.e., 120 interviews) will be selected. A proportion (40% and 20% for the main trial and pilot, respectively) will be double checked to calculate inter-rater reliability. Adherence will be determined by how closely the moderator follows the protocol (expressed as a percentage), and competency will be calculated by a mean score for each competency dimension.

#### Eligibility criteria

The micro-interventions are intentionally designed to be universally applicable, therefore children will not be screened for the presence or absence of positive body image. Eligible participants are; English-speaking children who are aged 4, 5 or 6 years old in Reception Class or Year 1 at primary school, with a respective parent/guardian located in Birmingham or Greater London. Participants will be excluded if they are a sibling of a child already recruited into the study (i.e., only one child per household can take part), and children who have complex special educational needs that would hinder their ability to enjoy partaking in the intervention(s) or the research process.

#### Recruitment

Recruitment will be led by a research agency (We Are Family) who have 25 + years of experience conducting research with children and their families. In the period of two to eight weeks prior to data collection, study information will be sent out to potential parents via We Are Family, which included details of participation and the purpose of the research: to evaluate the impact of children’s media on children’s wellbeing and self-esteem. Parents were not told the media being tested was Blippi. Parents of eligible children will be recruited based on three quotas: (i) an equal number of girls and boys, (ii) an equal number of children in Reception and Year 1, and (iii) at least 20% of children belonging to ethnic minority groups. Interested parents will be asked to complete a brief screener questionnaire including demographic information (e.g., age, ethnicity, employment status, socio-economic status) and eligibility criteria. If eligibility criteria are met, they will be asked to provide digital informed consent for them and their child to take part in the study. Once consent is gained, they will progress into the study. Those that do not consent will be thanked for their interest and will not proceed. Participants will then be randomised into one of four conditions by We Are Family using a spreadsheet detailing the block allocations. Following allocation, We Are Family will give parents the details of the location and time for the data collection and media screening sessions.

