## Method

### Study design

A 4-armed randomised controlled trial (RCT) will be conducted to evaluate two media micro-interventions: an approximately 15-minute positive body image episode and a 3-minute positive body image music video. Participants will be randomised using block randomisation, stratified by gender and year group into one of four conditions: (i) 15-minute episode intervention, (ii) 15-minute episode control, (iii) 3-minute music video intervention, or (iv) 3-minute music video control. Randomisation blocks will be in groups of four. The primary outcome for intervention effectiveness is body appreciation, assessed among children pre- and immediately post-intervention and at one-week follow up (T1, T2 and T3). The secondary outcomes for intervention effectiveness are functionality appreciation and weight bias, which will also be assessed among children at T1, T2 and T3. Parents and children will report on intervention acceptability at T2, and parents will report on media re-watch at T3. Parents will provide demographic information for them and their child (T0). A diagram of the research process is presented in Fig. 1.

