### Procedure

We Are Family will be responsible for contact with parents and organising study logistics (e.g., booking venues). The data collection and media screening sessions will be conducted face-to-face, in person with a team of moderators trained to deliver the research protocols (by KG and NC). There will be approximately 12 children with one of their respective parents per session. At T1, participants will arrive and be welcomed to the venue. The venue includes an initial waiting area and a main space where the child-interviews will take place. The main space will comprise of 12 booths around the edge, each with a table and two chairs, including a chair placed outside the booth for each parent to sit on. Once welcomed, participants will engage in five minutes of group play, facilitated by a moderator, to allow children to relax and become familiar with the environment. Next, participants will engage in a brief play activity with their allocated moderator to act as an ice breaker to the interview schedule. A moderator will complete the pre-interview (T1) with their assigned child (i.e., one moderator to one child) while their parent is encouraged to sit outside the booth. The pre-interview will commence with the child providing verbal assent (they will be told what to expect of the session and asked if they are happy to take part) and is expected to last up to 15 min.

As soon as the child has completed their interview, they will be given a tablet and two sets of headphones (one for the child and one for the parent) and asked to watch their assigned media together however they choose (e.g., sat on the floor, standing, on a chair). The moderator will remain close to the booth to provide any assistance if needed but will primarily be noting down any observations (e.g., engagement levels). Those in the music video conditions will be instructed to watch a 10-minute neutral video (i.e., Numberblocks) on a tablet, before they view their music video. This is to ensure each condition moves on to the post-interview at roughly the same time.

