### Statistical analyses

At trial completion, the data will be entered into SPSS, cleaned, screened and the T2 acceptability data separated out for concealment purposes. The concealed dataset will be delivered to the statisticians to conduct analyses.

The primary analysis will be on an Intention-to-Treat (ITT) basis inclusive of all randomised participants who provide some outcome data either immediate post-intervention (T2) or at follow-up (T3). Conclusions will be drawn from the ITT analysis set. In addition, a supplementary per-protocol analysis set, excluding any protocol deviations, will be undertaken. Prior to inferential analysis there will be a validity and verification assessment for data veracity. The primary outcome measure is body appreciation with endpoint being body appreciation immediate post intervention (T2). The primary analysis will be an analysis of covariance comprising randomised arm and body appreciation at T1 as a covariate. This model will include a baseline by covariate interaction term if necessary for model validity. Underpinning assumptions will be assessed for model validity and remedial action taken if required (e.g., robust homoscedasticity corrected analyses or bootstrap approaches as deemed necessary to ensure valid statistical conclusions). If the data is highly discrete to the extent of potentially compromising statistical conclusions, then the linear link function will be replaced by a more appropriate link function (e.g., ordinal logistic regression or negative binomial regression). If the baseline by covariate interaction term is deemed important then a follow-up Johnson-Neyman analysis of covariance will be used. These analysis of covariance models will compare (i) music intervention and music control using the data from the two appropriate arms, and (ii) 15-minute episode intervention and 15-minute episode control using the data from the two appropriate arms. Effect sizes, 95% Confidence Intervals and standardised effects will be reported as appropriate.

The above analyses will be extended to assess any moderating effects by gender, and any moderating effects by year group.

Secondary exploratory analysis will compare the 15-minute intervention and music intervention using the data from the two appropriate arms using the same methodological process.

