#### Qualitative analysis

Content analysis will be used for all open-ended questions (e.g., functionality appreciation and child and parent acceptability).

For functionality appreciation, two checkers (KG and HS) will independently assess children’s responses at each time point (T1, T2 and T3), determining which are valid based on the theoretical framework and conceptualisation of functionality appreciation ([52]). A valid response should fit into one of the six defined domains: (1) bodily senses and sensations (e.g., see, hear, smell), (2) creative endeavours (e.g., drawing), (3) internal processes (e.g., breathing), (4) physical capacities (e.g., playing games, sports), (5) communicating with others (e.g., hugging) and (6) self-care (e.g., brushing teeth), through importantly through the worldview of a child. Duplicate responses (e.g., walk and walking) will be collapsed and counted as one. Invalid responses include simply naming body parts (e.g., legs, arms) or non-sensical responses that do not fit the categories listed above. We will calculate a two-way mixed-effects, single-rate, absolute agreement ICC [65] to indicate if scoring is consistent between raters. A score of at least 0.75 indicates good reliability [65]. A total score for functionality appreciation will be the sum of valid responses, with higher scores indicating higher functionality appreciation.

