### Data management, data availability and sharing

Each participant will be given a unique participant ID for the purpose of matching responses over time. Anonymous data from participants (children and parents) from each timepoint (T1, T2 and T3) will be collected via paper and pen and entered into SPSS by members of the research team (HS, KG). The data file will be stored on a university approved cloud storage (e.g., OneDrive) and hard copies stored in a locked cabinet in line with the university’s policy. Hard copies will be screened for personal information and anonymised if required. The data file will be screened for data quality including completeness. Digital consent data and personal identifiers (e.g., participant contact details) will be collected by the research agency and kept securely until the end of the project; this information will not be shared with the authors. Audio recordings will be securely uploaded, cross-referenced and deleted once fidelity checks and inter-rater reliability assessments have been completed and resulting paper has been published.

An independent data monitoring committee will not be used as this project is deemed low risk and data collection will take place in a short period (a few weeks). Further, research team members who are not be concealed from condition allocation (i.e., not the statisticians) will review the data as it accumulates to assess for risk. The pilot also allows for a safety assessment of the trial.

The funder and the research agency will not have access to the raw data and all parties have a data processing agreement in place. Anonymised data will be made available upon reasonable requests for non-commercial use. Requests should be made to the project lead and corresponding author (NC).

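### The two people who judge which functionality answers are valid also enter the arm-revealing T2 data, and the article describes only the statisticians as concealed

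*Protocol article*

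**What the plan says.** **Concealment.** Under Statistical analyses, the file goes to the statisticians with "the T2 acceptability data separated out for concealment purposes". Under Data management, data availability and sharing, "research team members who are not be concealed from condition allocation (i.e., not the statisticians) will review the data as it accumulates" to assess risk. No section describes masking of the moderators or of the people who code answers. Parents are told the explicit aims and their condition only in the debrief after the T3 interview (Procedure).

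**Coding.** Under Qualitative analysis, two checkers "will independently assess children’s responses at each time point (T1, T2 and T3), determining which are valid". They use six defined domains, collapse duplicates and report an ICC for agreement. The number of valid answers is the functionality appreciation score, one of the two secondary effectiveness outcomes. The data management section gives the same two sets of initials for the staff who enter child and parent data from all three time points.

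**Eliciting.** During the viewing, "The moderator will remain close to the booth to provide any assistance if needed but will primarily be noting down any observations" (Procedure). The T2 interview follows at once, with a moderator.

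**Allocation.** After screening, "Once consent is gained, they will progress into the study", and then "Participants will then be randomised into one of four conditions by We Are Family using a spreadsheet detailing the block allocations" (Recruitment). The same agency leads recruitment, contacts parents and books venues. Under Study design, "Randomisation blocks will be in groups of four".

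**The concern.** The functionality score rests on human calls: whether an answer fits a domain, is nonsensical, or repeats another. The T2 acceptability material covers what the family watched, what they liked and what the child learned. The plan withholds it from the statisticians for concealment, so it treats that material as revealing the arm. The coders, however, are the people who enter it.

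Generosity applied equally to all arms would largely cancel in an intervention-control comparison. Generosity that depends on arm goes straight into the estimated effect. Both checkers also reviewed the intervention storyline (Table 2), so they know which messages the children were meant to absorb.

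The primary outcome is exposed in a different way. It needs no scoring judgement, because the child stands on a labelled shape. But a 4- to 6-year-old gives the answer in a one-to-one interview with an adult who may have seen what was on the screen.

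**Working it through.** **1. Roles side by side**

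| Task | Who | Route to knowing the arm | Section |
|---|---|---|---|
| Validity coding, T1 to T3 | Two team members | Same two enter all child and parent data, including T2 acceptability | Qualitative analysis; Data management |
| T2 interview | A moderator | A moderator stays near the booth during viewing; not stated to be a different person | Procedure |
| Allocation | Recruiting agency | Holds the block spreadsheet | Recruitment |
| Analysis | Statisticians | Acceptability data removed first | Statistical analyses |

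Only the last row has a stated concealment step.

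**2. The plan's own sample size, to fix the precision.** Inputs (Statistical power and sample size): two-sided alpha 0.05, 90% power, d = 0.3, r = 0.75.

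n per arm = 2(z₀.₉₇₅ + z₀.₉₀)²(1 − r²)/d² = 2 × (1.960 + 1.282)² × 0.4375/0.09 ≈ 102.2, rounded up to 103. The article states 103. The second scenario (d = 0.25, r = 0.8, 80% power) gives 91 against the stated 92. Both agree within rounding, so the design variance is 1 − r².

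**3. Standard error at the 105 per arm aimed for.**

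SE = √(1 − 0.75²) × √(2/105) = 0.6614 × 0.1380 = 0.091 SD.

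**4. False-positive rate if a bias b is added to a true null.** The values of b are assumptions; the article gives none.

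Rate = P(Z > 1.96 − b/SE) + P(Z < −1.96 − b/SE)

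| Assumed b (SD) | b/SE | False-positive rate |
|---|---|---|
| 0 | 0 | 5% |
| 0.05 | 0.55 | 8.5% |
| 0.10 | 1.10 | 19% |
| 0.15 | 1.64 | 38% |
| 0.20 | 2.19 | 59% |

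Applying this to functionality appreciation further assumes that r = 0.75, set for the primary outcome, also holds there.

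**5. Block predictability.** Each block of four holds one slot per arm. Someone who knows the earlier allocations in the stratum guesses the exact arm correctly with probability (1/4 + 1/3 + 1/2 + 1)/4 = 0.52, against 0.25 by chance. For intervention versus control the figure is (1/2 + 2/3 + 2/3 + 1)/4 = 0.71, against 0.50. The fourth slot is always certain. These figures describe predictability of allocation, not bias in an outcome.

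**The case against.** Several safeguards are stated and count. After the pilot, the moderator guide was fixed in part to verbatim wording, the order of the weight bias images was randomised, comments during that task were stopped, and ticks, crosses and red pen were dropped. Filler items are used and praise is directed at effort. All interviews are audio recorded and a sample is audited for adherence. Coding has predefined domains and two independent raters. These steps reduce cueing and idiosyncratic scoring. They do not mask anyone, and an ICC measures agreement, which two raters leaning the same way would also show.

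Four stronger readings are tempting and are not supported:

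- **That the T2 interviewer is the person who watched the viewing.** The Procedure section says only that a moderator conducts T2. The one-to-one set-up makes it likely and nothing prevents it, but it is inferred. Headphones limit what a bystander hears, not what is seen.
- **That the checkers will know the arm when they code.** The article does not say how answers are presented to them. It gives them roles that make such knowledge possible. The SPIRIT checklist (Supplementary File 2) is not shown and may say more.
- **That the agency's spreadsheet biases the outcomes.** It bears on who enters which arm. Allocation follows consent, the agency has no access to raw data, and the article does not say whether upcoming rows are visible.
- **That 19%, or any single figure, is the expected error rate.** It reflects only the bias assumed.

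**Conclusion.** The point holds in a limited form. By the roles stated, a judgement-based secondary outcome can be coded by people who have handled data the plan itself regards as arm-revealing, and only the statisticians are described as concealed. That is a possible route to bias; the article gives no evidence that bias will occur, and its size cannot be estimated from it. The range of 8.5% to 59% shows only that, with an SE of 0.091 SD and a planned effect of 0.3 SD, quite small arm-dependent shifts would matter.

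Two lesser points stand beside it: the T2 interviewer is not required to be someone who did not observe that child's viewing, and fixed blocks of four in the recruiter's hands make part of the sequence predictable. The latter is limited by consent coming first, although allocation still precedes attendance and the T1 interview.

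**What to change.** **Main change, no new staff.** Export functionality answers with ID, arm and time point removed, in shuffled order, and have both checkers score them before acceptability data are entered or opened. Alternatively, have another existing team member enter the acceptability data. Shuffle whole answer sets (one child at one time point), so that duplicates can still be collapsed within a set, and let someone other than the checkers keep the linking key. The cost is a little preparation time. Some answers, for example about dancing or tooth-brushing, may still hint at the arm; the direct cues are gone.

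**Secondary changes.**

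- Where the moderators present permit, have T2 conducted by one who did not observe that child's viewing, and state that acceptability is asked after the outcome measures. The cost is some lost rapport, which is a real trade-off at this age.
- Use varied block sizes (for example 4 and 8), and have the list held by someone independent of both recruitment and analysis. It should not be a trial statistician, since that would risk unmasking the one concealed group. The cost is a small administrative step at each allocation.
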